## A prior power analysis was performed to estimate the sample size needed in this study using G*Power. Previous studies in CHF have shown that mean differences in HRQOL between patients who received a psychosocial intervention and the usual care ranged from 0.11 to 0.68 (42). For ACT interventions targeting HRQOL, a recent review meta-analysis reported a mean effect of 0.48 for the clinical and non-clinical population, ranging from 0.37 to 1.55 when those who received the ACT intervention were compared to the active control, not including CBT (43). Thus, an estimated effect size of 0.50 was adopted across the above reviews. Targeting that effect size at a power of 0.8 with a prior power calculation, a minimal sample size of 128 is required to detect the difference between the ACT group and CE groups. Considering a weighted dropout rate of 16% for those participating in an ACT intervention indicated in a recent meta-analysis (44), and given group-setting and patient-caregiver dyadic participant requirements for the interventions, the total sample size was increased to 160 patient-FC dyads, accounting for an anticipated dropout rate of 20%.

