# Randomization and blinding

## In this study, allocations with a ratio of 1:1 will be performed through an online randomization program (<https://www.randomizer.org/>) by an independent researcher, who will be excluded from any other activity throughout the intervention. The unit of randomization is the patient-FC dyad. The randomization list will be stratified by the type of relationship between the patients and caregivers (e.g., spousal relationship vs. non-spousal relationship) with a block size of 4 or 6. The allocation sequence will be printed and sealed separately in opaque envelopes by the randomizer.

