## The staff nurses in the study hospital will enroll dyads of patients and caregivers. After the baseline assessment is completed, the dyad’s registration data will be given to the research coordinator. The research coordinator will open the envelope and then enter the data into the database and assign dyads to interventions. The participants will be informed of their allocation status via smartphone when the research coordinator plans to schedule the first session.

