# Statistical analysis

All quantitative data collected from the participants will be numerical coded, and analyzed utilizing IBM SPSS 27. Baseline sociodemographic and clinical data will be used using medians, proportions, and counts for categorical data; while means, standard deviations (SDs), skewness, and kurtosis will be used for continuous variables for participants in two groups. Differences in the participants’ characteristics at baseline will be explored using an independent T-test or Mann-Whitney U test for continuous variables, and Chi-squared or Fisher’s Exact test for categorical variables. The primary outcome and secondary outcomes will be summarized using means with SDs for the ACT group and CE groups. Randomized testing at baseline between the study groups will be performed to identify potential covariates. The differences in these outcomes between the ACT group and the CE groups over time will be analyzed using generalized estimating equations (GEE) which account for missing data at random. If any covariance is detected in the baseline comparison, it will be adjusted in the analysis of the effects of the intervention. Subgroup analysis will be adopted for specific factors (e.g., intervention completion and non-completion). The level of statistical significance is predetermined at p<0.05 (two-tailed). The intention to treat principle will be applied by comparing the ACT group with CE groups as randomized despite adherence to the intervention. Cohen’s d will be calculated to estimate effect sizes of between-group comparisons.

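### The only subgroup factor named, intervention completion, arises after randomisation, so results within completion strata are liable to be biased; the intention-to-treat comparison is unaffected

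*Protocol*

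**What the plan says.** In the Statistical analysis section, the protocol states: "Subgroup analysis will be adopted for specific factors (e.g., intervention completion and non-completion". No baseline factor is named as a subgroup. The type of patient-caregiver relationship (spousal or not) appears under Randomization and blinding, but only as a stratification factor. The section does not define completion. Nor does it say whether the contrast is ACT against CE within each stratum, or completers against non-completers.

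The same section fixes the main comparison: "The intention to treat principle will be applied by comparing the ACT group with CE groups as randomized despite adherence to the intervention".

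On timing, Randomization and blinding says: "The participants will be informed of their allocation status via smartphone when the research coordinator plans to schedule the first session". All sessions therefore come after allocation. The same part of the protocol states that dyads and interventionists are not blinded. Under Outcomes, participants who discontinue are still encouraged to be assessed, so both strata can hold outcome data.

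**The concern.** A subgroup analysis asks whether the treatment effect differs between kinds of participant, and it relies on randomisation holding within each kind. That works for a factor fixed at baseline. Completion is not such a factor: it follows allocation and may be influenced by the arm and by how the dyad is faring.

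The design leaves room for both influences. Dyads know their arm. ACT sessions are mostly experiential group work with a short education part, led by two facilitators; CE sessions are didactic, led by one nurse. Attendance is required of the pair, so the circumstances of either member can affect it, and the HRQOL of both members is the primary outcome. ACT completers and CE completers need not be alike in prognosis.

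At stake is a secondary result that could show ACT working in completers and failing in non-completers when it has no effect at all, or the same effect in everyone.

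**Working it through.** **Inputs from the protocol.** Planning effect: "Thus, an estimated effect size of 0.50 was adopted across the above reviews". Significance level: "The level of statistical significance is predetermined at p<0.05 (two-tailed". Sample size: "a minimal sample size of 128 is required to detect the difference between the ACT group and CE groups" at power 0.8, then "the total sample size was increased to 160 patient-FC dyads, accounting for an anticipated dropout rate of 20" (per cent). Allocation is 1:1.

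**The plan's own figure.** A two-sample t-test with d = 0.50, two-sided alpha 0.05 and power 0.80 needs 63.77, rounded up to 64 per arm, so 128 in total. Then 128 / (1 − 0.20) = 160. Both figures reproduce, and neither depends on the subgroup analysis. The value 0.50 serves below only as a yardstick.

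**Assumptions not in the protocol.** Completion is 80% in each arm, borrowing the 20% anticipated dropout because no non-completion rate by arm is given. Let a be the correlation of the tendency to complete with prognosis, and b the correlation of prognosis with outcome (SD 1). Selection acts only in ACT, better-prognosis dyads complete, and the true effect is zero.

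**Formulas.** The standard normal density at the 20% cut (0.842) is 0.280.

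- Completers, ACT − CE: a × b × 0.280 / 0.8 = a × b × 0.350
- Non-completers, ACT − CE: −a × b × 0.280 / 0.2 = −a × b × 1.400
- Completers − non-completers within ACT: a × b × (0.350 + 1.400) = a × b × 1.750

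| a = b | Completers, ACT − CE | Non-completers, ACT − CE | Completers − non-completers in ACT |
|---|---|---|---|
| 0.3 | 0.09 × 0.350 = 0.03 | −0.13 | 0.16 |
| 0.5 | 0.25 × 0.350 = 0.09 | −0.35 | 0.44 |
| 0.7 | 0.49 × 0.350 = 0.17 | −0.69 | 0.86 |

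Simulation of 2,000,000 dyads per scenario agrees: 0.032, 0.089 and 0.171 for completers; −0.130, −0.351 and −0.683 for non-completers; 0.161, 0.444 and 0.853 within ACT. The intention-to-treat difference was 0.00 each time.

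**Worst case.** If exactly the worst-prognosis 20% of ACT dyads leave, a = 1. The completer difference is then 0.350 × b = 0.105, 0.175 and 0.245 for b = 0.3, 0.5 and 0.7, which is 21% to 49% of 0.50. The moderate range, 0.03 to 0.17, is 6% to 34%.

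**When the between-arm bias vanishes or persists** (simulated, b = 0.5, true effect zero):

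- Completion unrelated to prognosis: 0.00 in both strata, within simulation error.
- Same selection (a = 0.5) and same 80% completion in both arms: 0.00 in both strata. Completers against non-completers within ACT still differ by 0.44.
- Same correlation (a = 0.5) but 70% completion in ACT and 90% in CE: +0.08 in completers and +0.15 in non-completers. Equal correlation alone is not enough; the rates must match too.

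**With a real effect.** If ACT adds 0.50 SD for every dyad and selection acts only in ACT (a = b = 0.5), completers show 0.59 and non-completers 0.15. A uniform effect then looks like one that depends on completion.

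**Precision.** With 80 dyads per arm and 20% not completing, the non-completer stratum holds 16 per arm at most. Power for d = 0.50 there is 0.28.

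**The case against.** The strongest reply is that this is one example in a supplementary analysis. The effectiveness comparison is made as randomised whatever the adherence, and discontinuers are followed up. The example is introduced as such, so other factors may be intended, and the full list and the definition of completion may properly sit in a statistical analysis plan that is not shown. The arms are matched on number and length of sessions, group size, platform and reminders, and the per-session payment described under Procedure does not distinguish them. Selection may therefore be similar in both.

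Much of this stands, and it limits what can be said. Four stronger readings are tempting, and the protocol does not support them:

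- A reader might infer that the trial's main result is compromised. It is not; the intention-to-treat sentence rules that out.
- A reader might infer that the completer result is certain to be biased, and upwards. Bias between arms needs completion to relate to prognosis and that selection to differ by arm. If better-prognosis dyads leave ACT, the sign reverses.
- A reader might infer that a hospital stay turns a dyad into a non-completer. Under Eligibility, sessions are only suspended and resume after discharge.
- A reader might expect a completer result to be presented as dose-response. Nothing in the text says so.

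What does not stand is the defence of the named example. Other factors would not repair this one, and leaving detail to a later document does not make completion a baseline factor. Matched logistics do not ensure equal selection when content differs and dyads are unblinded.

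**Conclusion.** The concern holds in a limited form. The only subgroup factor the protocol names is a post-randomisation variable, and no contrast built on it can be read as a randomised effect of ACT or as true effect modification. It is liable to bias rather than certain to be biased, and the fault is confined to this supplementary analysis.

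The size depends on assumptions the protocol does not supply: 20% non-completion, selection in ACT only and the correlations used. On these, moderate selection shifts the completer contrast by a modest fraction of the planning effect, and only the extreme case approaches half of it. The non-completer and within-arm contrasts can be distorted much more. This should be corrected before analysis, but it does not threaten the primary conclusion.

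**What to change.** 1. Restrict subgroup analyses to baseline factors, each tested by a treatment-by-factor interaction. Start with the existing stratifier, spousal against non-spousal relationship.
2. Replace the completion subgroup with a supplementary complier-average causal effect that uses randomisation as the instrument, with completion defined in advance as a number of sessions attended.
3. State its exclusion assumption: allocation to ACT has no effect in dyads who fall short of the cut. This is open to doubt because partial attendance may itself have an effect.
4. If completers and non-completers are still tabulated, label the comparison descriptive and non-causal.

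The cost is a change of wording and one extra analysis using session attendance. The sample size does not change. The estimate will be less precise: with 80% completion in ACT and no ACT received in CE, dividing the intention-to-treat difference by 0.8 widens the interval by about 1 / 0.8 = 1.25, treating the completion rate as known. If the exclusion assumption fails, this estimate is biased too, so it should stay supplementary.

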**Ethical considerations**

Ethical approval for this study was given by the institutional review board (IRB) of the Hong Kong Polytechnic University (reference: HSEARS20210225006; 23-Apr-2021) and the Taihe hospital (Version 3; reference: 2022KS013; 3-Jun-2022;). Oral consent and verbally recorded informed consent will be obtained from each patient and family caregiver before a baseline assessment and randomization are conducted. Participation in the study is completely voluntary for CHF patient-caregiver dyads, and they are free to withdraw from the study at any point without consequences. Participants' identities and data, including information collected and video/audio records, will be kept confidential and anonymous to safeguard their privacy. Only authorized personnel will be allowed access to the data for analysis purposes.

